### Randomization and allocation

Following baseline assessment and registration, patients will be randomized in a 2: 1 ratio to either the TCM-eRhab program or to the normal usual care control group, using a computer-generated randomization list. Randomization will be overseen by research assistant, who will have no direct involvement in implementing the trial. Randomization is stratified by clinical center.

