### Primary outcomes

#### Quality of life

Quality of life will be measured subjectively using the Quality of Life Questionnaire-Core (QLQ-C30), which as a core questionnaire has been used in a wide range of cancer clinical trials [11]. It is supplemented by disease specific modules. Categories include functional scales, global health status and QOL scale, in addition to several single-item symptom measures [12, 13]. In the current study, QLQ-C30 will be collected via online app with patients at baseline, week 2, 4 and 6 during intervention or usual care phase (Table 3).

**Table 3 Tab3:** Study assessment procedures and timetable

Visit schedule	pre	Treatment phase			Follow-up phase		
Study phase	Baseline testing	T1	T2	T3	T4	T5	T6
Week/year	Baseline	Week 2	Week 4	Week 6	1 year	2 years	3 years

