#### Self-reported psychological stress

##### The Self-Rating Anxiety Scale (SAS)

The scale includes 20 items and have four grades (Grade I-IV), ranging from I, which considers anxiety from normal, to Grade IV, which describes the most severe anxiety of the patients [14].

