#### Sample size

Previous studies evaluating TCM-eRhab program for early-stage CRC patients reported a mean difference of 66.1 ± 10 points after the intervention on the QOL-C30 scale. In addition, the evidence reported on the average of scores of QOL-C30 scale for CRC patients with early-stage was 61.5 ± 10 points. In order to provide 80% power to detect this clinically meaningful difference, using a two-sided test with alpha = 0.05 and assuming that 15% of patients opt out, we need to approach approximately 210 patients (TCM-eRhab intervention group:140 patients, Control group: 70 patients).

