### Statistical analysis

Analysis of the study will be performed using SPSS statistical software package, version SPSS26.0 (Chicago, IL, USA) by the “intention-to-treat” principle, therefor all randomized patients satisfying eligibility criteria will be included in the efficacy analysis. A comparison of demographic, social and clinical characteristics will be carried out for each arm. The primary analysis of the QLQ-C30 questionnaire and Self-reported psychological pressure scales is the domain-averaged difference in scores between TCM-eRhab intervention group and usual follow-up group after intervention. Difference in these variables between the intervention and control groups will examined using either chi-square tests or analysis of variance. To examine whether anxiety, depression and clinical syndromes are the prediction factors of metastasis after intervention, modelling will be performed in Stata.

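### The stated primary comparison of post-intervention scores names neither the baseline score nor the centre stratum, a valid but inefficient choice

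*Protocol article*

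**What the plan says.** The Statistical analysis section of the protocol article takes as primary the domain-averaged difference between arms, after the intervention, in QLQ-C30 and the psychological scales. It then says that differences in these variables "will examined using either chi-square tests or analysis of variance". No baseline covariate, change score, visit term or centre term is mentioned.

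Elsewhere the article shows what is available:

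- Quality of life section: "QLQ-C30 will be collected via online app with patients at baseline, week 2, 4 and 6".
- Table 3: the same four time points for SAS, SDS and FCRI.
- Randomization and allocation: "Randomization is stratified by clinical center".

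The Sample size section works from two mean scores with a common SD and no baseline correlation, "using a two-sided test with alpha = 0.05". That fits an unadjusted comparison of post-intervention scores.

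**The concern.** A patient-reported score usually correlates with the same patient's score six weeks earlier. A comparison that uses only the later score leaves that predictable variation in the error term, so the confidence interval is wider and power lower than the collected data allow. Centre was used to balance the arms. Leaving it out of the model tends to make the standard error slightly too large, and so the test somewhat conservative.

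The article names a method rather than leaving it open, so this is a point about a stated choice and not about missing detail. The Discussion describes willingness to take part as a major worry for enrolment. Precision that can be had without more patients is therefore worth taking.

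**Working it through.** **Inputs**

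- Intervention mean: the Sample size section says that previous studies "reported a mean difference of 66.1 ± 10 points after the intervention on the QOL-C30 scale". Although worded as a difference, 66.1 can only serve as a post-intervention mean.
- Reference mean: "the average of scores of QOL-C30 scale for CRC patients with early-stage was 61.5 ± 10 points".
- Implied difference: 66.1 − 61.5 = 4.6. SD 10.
- Two-sided alpha 0.05, 80% power, 2:1 allocation, 15% loss, 140 + 70 = 210 patients (Sample size section).
- Correlation r between baseline and week-6 score: not in the article. Assumed values are 0.3, 0.5 and 0.6.
- Week 6 as the time point: inferred from Table 3. The Statistical analysis section says only that it is after the intervention.

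**The plan's own figure**

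Control-arm size for an unadjusted comparison at 2:1:

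n = (1.960 + 0.842)² × 10² × (1 + 1/2) / 4.6² ≈ 55.6, so 56.

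That gives 56 + 112 = 168 evaluable patients, and 168 / 0.85 = 197.6, so 198. The stated 210 is about 6% larger. It follows exactly from a 20% loss (168 / 0.80 = 210), not from the stated 15%. The difference is on the safe side and is a separate matter.

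**Power without baseline**

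After 15% loss, 140 × 0.85 = 119 and 70 × 0.85 = 59.5, taken as 59.

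SE = 10 × √(1/119 + 1/59) = 10 × √0.02535 = 1.592

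4.6 / 1.592 = 2.889

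Power from the noncentral t distribution with 176 degrees of freedom is 81.9%.

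**Power with baseline as covariate**

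The ANCOVA approximation multiplies the variance by (1 − r²), so the residual SD is 10 × √(1 − r²).

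| r (assumed) | Variance removed | Residual SD | SE | 4.6 / SE | Power |
|---|---|---|---|---|---|
| 0 (unadjusted) | 0% | 10.00 | 1.592 | 2.889 | 81.9% |
| 0.3 | 9% | 9.54 | 1.519 | 3.028 | 85.4% |
| 0.5 | 25% | 8.66 | 1.379 | 3.336 | 91.3% |
| 0.6 | 36% | 8.00 | 1.274 | 3.611 | 94.9% |

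**The same gain as sample size**

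For 80% power including 15% loss, the unadjusted total of 198 falls as follows:

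- r = 0.3: 51 × 3 = 153, and 153 / 0.85 = 180.
- r = 0.5: 42 × 3 = 126, and 126 / 0.85 = 148.2, so 149.
- r = 0.6: 36 × 3 = 108, and 108 / 0.85 = 127.1, so 128.

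**What cannot be computed**

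The article gives no figures from which to size the gain from a centre term or from the week 2 and week 4 scores. Its planning inputs are for QLQ-C30 only, so the table does not carry over numerically to SAS, SDS or FCRI.

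**The case against.** The strongest reply is that little is broken. Randomisation makes an unadjusted comparison of post-intervention scores unbiased, and chance imbalance at baseline is sampling error that the confidence interval already covers. Power without adjustment, about 82%, still exceeds the 80% target. Analysis of variance does not strictly rule out a centre factor or a repeated-measures form, and such terms are often left to an analysis plan. All of this stands, and it limits the point to efficiency. It does not remove it: the article names a method, and neither baseline nor centre is in it.

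Two stronger readings are tempting but not supported.

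- *Patients without a week-6 score are dropped.* A reader might infer this because a simple analysis of variance needs an outcome for each patient and 15% are expected to opt out. The article does not say so. It promises to include all eligible randomised patients and is silent on missing scores, which an unseen analysis plan may cover. Nor does it say when patients leave, so the number who could supply week 2 or week 4 scores is unknown.
- *SAS grades will be tested by chi-square.* A reader might infer this from the description of the instrument: "The scale includes 20 items and have four grades (Grade I-IV". But the primary analysis is defined on scores. The pairing of chi-square with analysis of variance can be read as categorical versus continuous variables, including the baseline characteristics mentioned just before. No text assigns chi-square to SAS.

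**Conclusion.** The point holds as one of lost precision. The stated primary comparison is valid and meets its power target on the plan's inputs, but it names neither the baseline score nor the stratification factor, both of which are available. For QLQ-C30, baseline adjustment would raise power from about 82% to about 85%, 91% or 95% at correlations of 0.3, 0.5 or 0.6, which removes 9%, 25% or 36% of the residual variance.

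The size rests on that assumed range, on a difference of 4.6 with SD 10, on 119 and 59 patients analysed, and on week 6 as the time point. The direction does not depend on the exact value: any appreciable correlation gives a gain. The article does not support a claim of bias, of an inflated false-positive rate or of an underpowered trial.

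**What to change.** State in the Statistical analysis section, or in the analysis plan:

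- Each primary scale is analysed as a continuous score at week 6 by ANCOVA with arm, baseline score and centre.
- Alternatively, a mixed model for repeated measures uses the week 2, 4 and 6 scores with the same adjustment and takes the week-6 arm difference as the primary estimate. This lets patients with partial follow-up contribute, in line with the stated intention-to-treat aim.
- The adjusted difference is reported with its 95% confidence interval.
- Chi-square tests are limited to categorical variables.

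The change is one of wording. The baseline scores, the later scores and the centre are already collected, and the sample size need not change. It should be made before outcome data by arm are seen.

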## Discussion

TCM-eRhab program as an online mind–body group therapy intervention has the potential to address complex constellation of symptoms. Meanwhile, TCM-eRhab program integrates treatment elements of TCM psychotherapy and modern psycho-oncology. By carrying out this randomized controlled trial, it will facilitate the development of current clinical practice towards innovative models of integrative Chinese and western rehabilitation and optimize the modern mind–body intervention methods.

The main objective of this study is to assess the evidence of TCM-eRhab program for improving CRC patient’s quality of life after radical surgery as well as benefiting their survival outcomes especially DFS. According to current ASCO guideline, promoting health condition, treating cancer related symptoms and preventing cancer recurrence are all major components of survivorship care for CRC patients. However, there is still lack of an effective and efficient intervention that could meet more patients’ needs at the same time. Thus, our study results will have profound meaning for the development an integrative intervention model of cancer survivorship care for CRC survivors.

This study will conduct online group therapy for patients which contains potentially unique therapeutic advantages such as encouraging expression, peer-support, coping skills, mindfulness practice and emotional expression. In addition, each patient will receive a comprehensive psychological, symptom and survivorship care needs assessment that is carried out at the beginning of the therapy, so that individualized TCM and supportive care plans can be integrated into the related session. So far, several studies have proved that education on lifestyle and health behavior has positive impact on CRC patients’ quality of life [20, 21]. To the best of our knowledge, the current study is one of the first to integrate methods and opinions of TCM into such education program and group therapy.

Experimental studies found that the combination of social interactions and cognitive stimulation regulated serum inflammatory factors, intestinal mucosal inflammatory factors and hypothalamic ghrelin levels [22, 23]. Some TCM herbal medicine, for example, Xiaoyaosan was found to be effective on preventing cancer cell progression and ameliorating gut dysbiosis through CRC mice model with chronic stress [24]. Our previous phase I trial also demonstrated that TCM-eRab intervention could modulate CRC survivors’ gut microbiome which had association with certain mental disorders. In the current trial, more mechanism on gut-brain axis interaction and CRC’s survival outcome are expected to be carried out.

There are some limitations on the current study design and certain obstacles for the administration of the clinical trial. First, as a behavioral study, it is unrealistic to conduct blind method, but we will use patient-reported outcome measurement to avoid investigator evaluation bias. Second, willingness to participate in the current trial is one of the major concerns for patients’ enrollment. According to an existing study, more than 60% CRC patients were not willing to participate in psychological intervention due to no perceived needs, older age and longer time since diagnosis [25]. Thus, in our study, we need to pay more attention on the balance between effectiveness of enrollment and population selection bias. Third, patients’ compliance of six-week intervention is also an important challenge for our study. We will record patients’ participation for each session and encourage them to comply with the protocol.

In conclusion, in this phase II randomized controlled clinical trial, we will evaluate the efficacy of an innovative model of online group psychotherapy, TCM-eRab on CRC survivors’ quality of life and survival outcomes after surgery. The implementation of the trial will help more CRC patients cope with their symptom burden and acquire guidance on healthy lifestyle by utilizing concepts and methods of TCM.

## Data Availability

All data of the clinical trial will be available under request to corresponding author ([name], [contact]) after the primary results being published.
